### 2.13. Data and Sample Collection and Analysis of Variables

#### 2.13.1. Data Collection

Data and biological sample collection will be conducted prior to the initiation of the nutritional intervention (baseline) and throughout the intervention during scheduled follow-up visits at 6, 12, 24, and 48 weeks. A comprehensive clinical assessment will be performed, encompassing the collection of anthropometric data (height, weight, body mass index), detailed records of patient medication, and evaluation of dietary intake using a 24 h dietary recall and Food Frequency Questionnaires (FFQs). Additionally, validated instruments will be employed to assess quality of life (CVEII-9) [Figure 2] and physical activity levels (IPAQ) [Figure 3].

The use of Mediterranean diet adherence questionnaires (PREDIMED) [Figure 4], the 24 h dietary record, and Food Frequency Questionnaires (FFQs) are useful tools for assessing adherence to the Mediterranean diet. However, they are not without limitations, as they may not capture inter-individual variability in diet or may be misinterpreted by subjects. Measurement of certain biomarkers that increase during a Mediterranean diet (such as carotenoids, n-3 fatty acids, and/or monounsaturated fatty acids) may be a more objective alternative to assess dietary adherence [13].

Body composition and functional changes will be analyzed using biochemical parameters associated with the underlying pathology and the patient’s general health status. Functional performance tests, including dynamometry, BIA, and nutritional ultrasonography, will be conducted to evaluate morphofunctional alterations. A comprehensive nutritional and morphofunctional assessment will be repeated three months following the conclusion of the dietary intervention.

Clinical remission will be evaluated using the Harvey–Bradshaw Activity Index (score < 5) and fecal calprotectin levels (<250 µg/g). At weeks 24 and 48, the radiological imaging study performed at baseline (e.g., MRI enterography or intestinal ultrasonography) will be repeated and/or an intestinal biopsy may be performed to objectively confirm remission of CD.

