## 2. Materials and Methods

### 2.1. Study Objectives

The primary objective of this clinical study is to determine the effectiveness and impact on body composition of implementing an ED for symptomatic remission in adult patients with active CD.

To achieve this objective, five specific aims are defined:To assess the improvement of clinical and inflammatory parameters related to the progression of the disease.To evaluate the incidence of sarcopenia through the assessment of muscle strength, function, and composition using functional tests, dynamometry, bioelectrical impedance analysis (BIA), and nutritional ultrasound.To determine the rate of improvement in the quality of life of patients and the disease remission by evaluating the Crohn’s Disease Activity Index (using the CVEII9 quality of life questionnaire and the Harvey–Bradshaw Index).To analyze the modifications in the intestinal microbiota resulting from the implementation of the ED.To examine the progression of clinical, anthropometric, analytical, and body composition parameters.

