### 2.4. Eligibility Criteria

#### 2.4.1. Inclusion Criteria

The following criteria must be met for inclusion in this study:Subjects of both sexes over 18 years of age.A diagnosis of active luminal CD with small bowel involvement, with or without colonic involvement, prior to study inclusion.Active symptoms of CD at the time of initiation of the nutritional intervention.Active disease, defined as a Harvey–Bradshaw Index (HBI) > 4 and an objective measure of disease activity, such as an elevated inflammatory marker (CRP > 5 mg/L or 0.5 mg/dL, or calprotectin ≥ 250 µg/g) and/or a radiological imaging test (MR enterography or intestinal ultrasound) or an endoscopic test (ileocolonoscopy or capsule endoscopy).Ability and willingness to adhere to one of the nutritional interventions.Capacity to complete and sign the informed consent form.

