### 2.11. Sample Size and Recruitment

Based on similar studies conducted primarily in pediatric populations, but also in adults [11,12], and taking into account the multiple outcomes to be obtained from the analysis of multiple variables, we estimate that, to achieve a significance level of 0.05 and a statistical power (β) of 0.8, a sample size of 48 patients per group would be required. Adjusting for a 5% dropout rate, we plan to recruit at least 50–55 patients per group to ensure the robustness of the analysis.

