### 2.12. Randomization and Blinding

Patients will be randomized in a 1:1 ratio after meeting the study inclusion and exclusion criteria. In the control group, patients will receive standard nutritional recommendations, whereas in the intervention group, they will follow a dietary strategy based on partial enteral nutrition combined with an exclusion diet, which has been shown to be effective in inducing remission, promoting mucosal healing, and serving as a rescue therapy for patients with inadequate response to biologic treatments.

Patients in the intervention group will be required to maintain this dietary strategy for 12 weeks, with structured follow-up visits at 6, 12, 24, and 48 weeks. Subsequently, patients should continue with the maintenance phase starting from week 13 onwards. Nutritional intake will be adjusted to ensure a balanced provision of macronutrients and essential micronutrients, prioritizing the inclusion of key substrates for short-chain fatty acid production while avoiding foods and additives with potential pro-inflammatory effects.

Simple randomization will be computer-generated and conducted by a member of the research team at the study site. Due to the nature of the intervention, neither patients nor research or medical staff will be blinded. Group assignment will be disclosed to patients at the moment of their participation acceptance.

Furthermore, to minimize the risk of bias, the clinicians from the Gastroenterology Department responsible for performing imaging assessments, as well as the translational researchers from the Biomedical Research Institute of Murcia (IMIB) in charge of analyzing blood, urine, and stool samples, will remain blinded to the dietary allocation of the study participants.

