### 2.15. Statistical Methods

All statistical analyses will be performed using SPSS software version 22.0, considering *p* < 0.05 as the threshold for statistical significance. A descriptive analysis of the variables will be conducted, providing point estimates and 95% confidence intervals. Continuous variables will be expressed as means and standard deviations or medians depending on the distribution of the data. Categorical variables will be reported as frequencies and percentages.

Comparisons of continuous variables will be performed using Student’s *t*-test (for two-group comparisons) or ANOVA (for comparisons involving more than two groups). Associations between categorical variables will be assessed using the chi-square test. Correlation analyses will be conducted using Pearson’s or Spearman’s correlation coefficients, depending on the normality of the variables under study. Relationships between multiple variables will be analyzed using multivariate statistical models.

Given the multiple outcomes to be assessed and the multiple comparisons to be analyzed, a Bonferroni correction (0.05/no. of comparisons as the significance level) will be also performed to avoid the risk of false positives.

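### Remission would be compared by an unadjusted chi-square although baseline HBI and calprotectin are collected; a baseline-adjusted remission test, supported by an adjusted full-scale HBI comparison, costs almost nothing and gains some power

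*Protocol article*

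**What the plan says.** The primary objective in section 2.1 is "to determine the effectiveness and impact on body composition of implementing an ED for symptomatic remission in adult patients with active CD". Section 2.13.1 gives the rule for remission: "Clinical remission will be evaluated using the Harvey–Bradshaw Activity Index (score < 5) and fecal calprotectin levels", the second bound being below 250 µg/g. Imaging is repeated, and a biopsy may be taken, at weeks 24 and 48 to confirm it.

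Section 2.15 gives general rules by type of variable. For categorical variables: "Associations between categorical variables will be assessed using the chi-square test". Continuous variables in two groups go to Student's t-test. Multivariate models are mentioned without an outcome, a covariate or a model form. A Bonferroni correction is added, with the number of comparisons left open.

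Entry requires disease activity: "Active disease, defined as a Harvey–Bradshaw Index (HBI) > 4", plus an objective sign of activity, which may be CRP, calprotectin, imaging or endoscopy (section 2.4.1). Table 1 schedules the HBI and the stool samples at baseline and at weeks 6, 12, 24 and 48. On size, section 2.11 says that "a sample size of 48 patients per group would be required".

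**The concern.** The two-group tests that section 2.15 names compare the arms without using where each patient started. For remission this matters in three ways.

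- Remission is an absolute threshold. A patient who enters with an HBI of 5 needs to lose one point to meet the HBI part; one who enters at 14 needs to lose ten. Baseline HBI may therefore predict the outcome, and randomisation is simple, so nothing in the design balances it.
- Section 2.4.1 lets a patient enter on CRP, imaging or endoscopy. Some patients may therefore already be below the calprotectin bound at baseline, so baseline calprotectin may also predict remission.
- A yes/no cut does not use the size of the change. A fall from 14 to 5 counts the same as no change.

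With about 48 evaluable patients per group, a Bonferroni level on top, and limited sample size and attrition listed among the weaknesses in section 3, information already collected should be used. What is at stake is the chance of detecting a real effect and the precision of its estimate.

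**Working it through.** **Inputs from the article.** 48 per group (section 2.11); "to achieve a significance level of 0.05 and a statistical power (β) of 0.8"; allocation 1:1 (section 2.12). The only between-arm remission rates are 75.6% v 45.1% (section 3). They come from a paediatric trial against exclusive enteral nutrition and are not stated to be the planning effect.

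**Assumed, because the article does not give them.** Two-sided testing, the HBI distribution, the control remission rate, the correlation between baseline and later HBI, and the Bonferroni divisor.

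**The plan's own figure.** Significance level and power alone do not fix 48, so it cannot be reproduced from section 2.11. At 75.6% v 45.1%, 80% power needs 40 per group without continuity correction and 46 with it. The figure 48 is taken as given.

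**Step 1: chi-square on the cut.** Power = Φ{[|p1 − p2|√n − 1.96√(2p̄(1 − p̄))] / √[p1(1 − p1) + p2(1 − p2)]}. With p1 = 0.756, p2 = 0.451, p̄ = 0.6035 and n = 48: (2.113 − 1.356) / 0.657 = 1.15, so power is 87.5%.

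**Step 2: the same shift on the full HBI scale.** If HBI is normal with equal SD in both arms and is cut at one point, the standardised difference is d = z(0.756) − z(0.451) = 0.693 + 0.123 = 0.82. The non-centrality is 0.817 × √(48/2) = 4.00 on 94 degrees of freedom, which gives a t-test power of 97.7%. The gain is about 10 points.

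**Step 3: an effect that gives the cut 80% power.** The treated rate is solved so that the chi-square has 80% power.

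| Control rate (assumed) | d | Chi-square | Full-scale t-test | Gain |
|---|---|---|---|---|
| 40% | 0.725 | 80% | 94.0% | 14 |
| 50% | 0.745 | 80% | 95.1% | 15 |
| 60% | 0.791 | 80% | 97.0% | 17 |

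Steps 2 and 3 give the range of roughly 10 to 17 points. It is not a bound. At 75% v 50% the t-test gains about 18 points (72.2% v 90.5%) and at 80% v 60% about 24 (57.2% v 81.4%). Simulations with skewed integer HBI scores gave about 7 to 20 points, depending on the scenario and the full-scale method. At an illustrative level of 0.005 (10 comparisons assumed), 75.6% v 45.1% goes from 60.3% to 86.6%.

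**Step 4: adjusting the remission test itself.** Simulated power over baseline correlations of 0 to 0.5, with remission as the HBI cut and adjustment for baseline HBI:

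| Rates | Chi-square | Adjusted logistic |
|---|---|---|
| 75.6% v 45.1% | 0.87–0.89 | 0.88–0.92 |
| 72.5% v 45% | 0.80–0.81 | 0.81–0.86 |
| 84.5% v 60% | 0.77–0.79 | 0.76–0.84 |

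The gain is nil at correlation 0, about 2 points at 0.3 and about 3 to 6 points at 0.5. Type I error was 0.044 to 0.060 for all methods.

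**What the figures leave out.** All of them concern the HBI component. The article gives no joint rates of HBI and calprotectin, so the gain for the two-part definition was not computed.

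**The case against.** A reader might infer that the plan tests disease activity only as an HBI cut and so gives up 10 to 17 points of power. The article does not support that. HBI is scored at every visit, aim 3 in section 2.1 names it, and the general t-test rule in section 2.15 could cover the score on its full scale. What stands is that nothing assigns that comparison, and that a t-test would still ignore the baseline value.

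It can also be said that section 2.15 ties no test to remission, that its multivariate models might include baseline terms, and that an article may leave model details to a fuller document. This is fair, and it rules out a complaint about missing detail. The point here is narrower: the one two-group test that is stated for a categorical outcome can be bettered with data already scheduled.

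Third, remission is what the objective asks about. To put an HBI difference in its place would change the question, drop the calprotectin component, whose laboratory analysts are blinded, and rest efficacy on a score taken without blinding (section 2.12). That objection stands in full, so the full-scale comparison belongs beside remission and not in its place.

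Finally, the entry bound and the remission bound meet, which might look like a flaw. They are complementary: active disease and its absence. Nor does chance imbalance make the chi-square invalid; the simulated type I error shows no such problem.

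**Conclusion.** The point holds as a modest, nearly free gain in efficiency. The stated comparison of a remission rate uses neither baseline HBI nor baseline calprotectin, and no baseline-adjusted comparison of full-scale HBI is assigned.

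The direction is firm and the size is not. Adjusting the remission test is worth about 0 to 6 points of power at 48 per group and 0.05, depending on a baseline correlation that the article does not give; requiring an HBI above 4 at entry may lower it. The 10 to 17 points describe the HBI component alone, under an assumed normal score and illustrative rates that are partly paediatric and against another comparator. They should not be read as the power that this trial loses on its two-part remission measure.

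**What to change.** In section 2.15:

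1. Keep remission, HBI below 5 with calprotectin below 250 µg/g, as the efficacy measure.
2. Replace the chi-square for it with logistic regression on treatment arm, adjusted for baseline HBI and log baseline calprotectin. Report a standardised risk difference with 95% CI, next to the plain remission rates by arm.
3. Add, as a named supporting analysis and not a replacement, a between-arm comparison of full-scale HBI adjusted for baseline HBI, by ANCOVA or a proportional-odds model, at the time point at which remission is tested.

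The cost is some wording and a few extra lines of analysis, with no new patients, visits or samples. Two small downsides belong to the supporting analysis: HBI is scored without blinding, and a score difference is less direct for clinicians than a remission rate.

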#### 2.13.2. Sample Collection and Storage

Biological samples, including blood, urine, and stool, will be collected at baseline (prior to the initiation of the nutritional intervention) and at scheduled follow-up visits at 6, 12, 24, and 48 weeks. Sample collection will adhere to standardized protocols to ensure the integrity and reproducibility of the analyses.

Blood samples will be collected via venipuncture into EDTA and serum separator tubes. Plasma and serum will be separated by centrifugation at 4 °C within 30 min of collection. Stool samples will be obtained using sterile containers and immediately aliquoted for microbiota, calprotectin, and metabolomic analyses. Urine samples will be collected using sterile procedures and processed within 1 h of collection. All biological materials will be aliquoted into cryovials and stored at −80 °C until further analysis.

Sample transportation from the collection site to the laboratory will be conducted using validated cold-chain logistics to maintain a temperature of 2–8 °C for short-term handling and ensure sample stability. Metadata associated with each sample (e.g., time of collection, participant ID, processing time) will be systematically recorded in a digital database for traceability.

To ensure long-term preservation, aliquots will be stored in a dedicated biobank facility under controlled conditions with continuous temperature monitoring and backup power systems. Samples will be retained for subsequent analyses, including but not limited to biochemical assays, genomic and proteomic studies, and microbiota profiling. All procedures comply with international ethical guidelines and Good Laboratory Practices (GLPs).

#### 2.13.3. Characterization of Quantifiable Analytical Parameters in Serum, Urine, and Stool

The following hematological, biochemical, metabolic, nutritional, and inflammatory parameters will be quantified in serum:Hematological and coagulation parameters: complete blood count (CBC) and coagulation profile.General biochemical profile: fasting glucose, electrolytes (sodium, potassium, chloride), nitrogenous compounds (urea, creatinine), mineral metabolism markers (calcium, phosphorus, magnesium), hepatic function enzymes (aspartate aminotransferase [AST/GOT], alanine aminotransferase [ALT/GPT], gamma-glutamyl transferase [GGT], alkaline phosphatase, total and direct bilirubin, lactate dehydrogenase [LDH], creatine kinase).Metabolic and endocrine markers: insulin, homeostatic model assessment for insulin resistance (HOMA-IR), C-peptide, and glycated hemoglobin (HbA1c).Lipid profile: total cholesterol, high-density lipoprotein cholesterol (HDL-C), low-density lipoprotein cholesterol (LDL-C), and triglycerides.Nutritional biomarkers: prealbumin, albumin, fat-soluble vitamins (A, D, E), trace elements (zinc, selenium), vitamin B12, iron, folate, ferritin, transferrin, and transferrin saturation index.Inflammatory biomarkers: C-reactive protein (CRP), erythrocyte sedimentation rate (ESR), and interleukin-6 (IL-6). Inflammatory markers will be quantified using high-sensitivity multiplex immunoassays to enhance precision and reduce inter-assay variability.

Analysis in fecal samples will include the following:Fecal calprotectin: a surrogate marker of intestinal inflammation, measured using enzyme-linked immunosorbent assay (ELISA) or equivalent high-sensitivity immunoassays.Analysis of the gut microbiota composition will be performed by 16S rRNA gene sequencing in stools. DNA extraction from stool samples will be performed using 200 mg of sample using the QIAamp DNA Stool Mini kit (Qiagen, Manchester, UK), following the manufacturer’s instructions. The concentration and quality of the DNA will be determined by the Agilent 2200 TapeStation system. To create the libraries, DNA samples (5 ng/µL) will be amplified using a primer, encoding the hypervariable regions V2-4-8 and V3-6, 7-9 of the bacterial 16S rRNA using the 16S Metagenomics Kit (Thermo Fisher, Waltham, MA, USA). The amplicons obtained will be purified using AMPure^®^ XP beads (Beckman Coulter, Pasadena, CA, USA) and, subsequently, the libraries will be created using the Ion Plus Fragment Library kit (Thermo Fisher, Waltham, MA, USA) and the Ion Xpress Barcode Adapters 1–16 kit (Thermo Fisher, Waltham, MA, USA) to add barcodes to purified amplicons. The libraries will be purified using AMPure^®^ XP beads (Beckman Coulter, Pasadena, CA, USA) and quantified by fluorescence. Sequencing of the libraries will be carried out using an Ion S5 platform. The results of composition, diversity, and richness will be analyzed using the QIIME2 platform, and functionality will be analyzed through the PICRUST software package (Version v2.6.2).

### 2.14. Data Management

An electronic Case Report Form (eCRF) will be used to systematically record all study-related variables. A structured data collection form will be designed and implemented in SPSS software for statistical processing. Upon completion of this study, all collected data will be reviewed and analyzed for inclusion in the final study report.

All study-related documents will be securely stored in the Principal Investigators Archive at the participating institution, under the custody of the Principal Investigators, until this study is completed. Once the study concludes, the documentation will be indexed and transferred to the central archive of the institution, in compliance with Good Clinical Practice (GCP) guidelines.

Data will be iteratively verified and corrected until the database is fully validated. Following data cleaning and validation, variables will be recoded and transformed (e.g., grouping, summation, composite indices) for further statistical analyses.

### 2.15. Statistical Methods

All statistical analyses will be performed using SPSS software version 22.0, considering *p* < 0.05 as the threshold for statistical significance. A descriptive analysis of the variables will be conducted, providing point estimates and 95% confidence intervals. Continuous variables will be expressed as means and standard deviations or medians depending on the distribution of the data. Categorical variables will be reported as frequencies and percentages.

Comparisons of continuous variables will be performed using Student’s *t*-test (for two-group comparisons) or ANOVA (for comparisons involving more than two groups). Associations between categorical variables will be assessed using the chi-square test. Correlation analyses will be conducted using Pearson’s or Spearman’s correlation coefficients, depending on the normality of the variables under study. Relationships between multiple variables will be analyzed using multivariate statistical models.

Given the multiple outcomes to be assessed and the multiple comparisons to be analyzed, a Bonferroni correction (0.05/no. of comparisons as the significance level) will be also performed to avoid the risk of false positives.

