## Abstract

**Background:** Crohn’s disease (CD) is an inflammatory bowel disease in which there is an alteration in the homeostasis and functionality of the intestinal mucosa accompanied by a dysbiosis of the commensal microbiota. The analysis of different dietary strategies to achieve CD remission and reduce gastrointestinal symptoms concludes that it is necessary to restrict the intake of ultra-processed products and to promote the consumption of those with anti-inflammatory effects that improve intestinal permeability and dysbiosis. **Methods:** Based on previous studies conducted in other cohorts, mainly pediatric, we propose an experimental, prospective, randomized study in patients with active CD who do not show improvement with conventional pharmacological treatment. The control group will receive standard nutritional recommendations while the intervention group will be prescribed an exclusion diet supplemented with enteral nutrition. **Results:** Patients in the intervention group are expected to exhibit increased lean body mass and reduced visceral fat, as measured by bioelectrical impedance analysis (BIA), alongside higher rates of clinical remission (CDAI), decreased inflammatory markers, and improved gut microbiota composition. Additionally, improvements in health-related quality of life are anticipated, as assessed by validated questionnaires. **Conclusions:** In the present project, we plan to conduct a detailed study to determine the potential of the exclusion diet for the treatment and remission of CD in adult patients, with the hypothesis that this nutritional intervention will be able to modify and improve intestinal dysbiosis, inflammatory status, and clinical and body composition markers in these patients.

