### 2.2. Design

This is an experimental, prospective, randomized study with matched data, including patients with CD who are either about to begin pharmacological treatment or are scheduled to have their medication changed due to an insufficient response and lack of positive disease progression. The pharmacological treatment will be prescribed based on clinical indications by the medical team at baseline and will not be influenced by whether the exclusion diet is implemented.

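### Section 2.15 names only a t-test or ANOVA for continuous outcomes measured at up to five visits, with no baseline adjustment, repeated-measures analysis or rule for skewed markers

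*Protocol article*

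**What the plan says.** The protocol article fixes the comparison of continuous outcomes in section 2.15: "Comparisons of continuous variables will be performed using Student’s *t*-test" where there are two groups, and ANOVA where there are more. The only other wording there that could cover an adjusted analysis is "Relationships between multiple variables will be analyzed using multivariate statistical models", which names no outcome, covariate or time term.

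Distribution is considered in two places in that section. For summaries: "Continuous variables will be expressed as means and standard deviations or medians depending on the distribution of the data". For correlations, the choice is between "Pearson’s or Spearman’s correlation coefficients, depending on the normality of the variables under study". No such rule is given for group comparisons.

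The trial has two arms, allocated 1:1 by simple randomisation (section 2.12). Visits are at baseline and at weeks 6, 12, 24 and 48 (section 2.13.1). Table 1 schedules BIA, the quality-of-life questionnaire and the blood, urine and stool samples at all five. Nutritional ultrasound and dynamometry are at baseline and weeks 12, 24 and 48. Body composition is part of the primary objective (section 2.1).

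Section 2.2 describes the design thus: "This is an experimental, prospective, randomized study with matched data". No matching of patients and no paired analysis is described anywhere.

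**The concern.** A plain two-group t-test at one visit uses neither the patient's baseline value nor the other visits. Measures such as lean mass differ much more between adults than they are likely to change in 12 weeks. For them the baseline value can explain most of the variance at follow-up, and a test that leaves it out can detect only large effects. That bears directly on the body-composition part of the primary objective, and the Abstract expects "increased lean body mass and reduced visceral fat, as measured by bioelectrical impedance analysis (BIA".

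Section 2.15 also leaves open whether the tested quantity is the follow-up value or the change from baseline. The two can give different answers from the same data. Patients and research staff are not blinded (section 2.12), so this choice is better fixed in advance.

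The inflammatory markers raise a separate question. CRP and calprotectin are commonly right-skewed, and a t-test on untransformed values of such a marker loses power. The only comparison methods named are the t-test and ANOVA.

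Finally, the reference to matched data in section 2.2 has no counterpart in the analysis. Simple randomisation does not match the arms. If repeated measures within patient are meant, section 2.15 names no method for them.

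**Working it through.** **Inputs from the protocol article.** 48 per group, significance level 0.05 (taken as two-sided) and power 0.8 (section 2.11); 1:1 allocation (section 2.12).

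**Inputs assumed.** Baseline-to-follow-up correlation ρ from 0.5 to 0.95; log-SD of a skewed marker from 1.0 to 1.5. The article gives neither.

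**The plan's own figure.** Section 2.11 gives no effect size, SD or event rates, so 48 per group cannot be rebuilt from its inputs. The dropout step is consistent: 48 / 0.95 = 50.5, or 51, within the stated 50 to 55.

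**Step 1: t-test on follow-up values.** Solving the two-sample t-test for 48 per group, two-sided 0.05 and 80% power gives a detectable difference of 0.578 SD.

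**Step 2: the alternatives.** Relative to the SD at one visit (taken as equal at baseline and follow-up), the effective SD is multiplied by √(1 − ρ²) for a baseline-adjusted analysis (ANCOVA) and by √(2(1 − ρ)) for a t-test on change. Multiplying 0.578 by each factor gives the detectable difference in SD. For example, at ρ = 0.9, 0.578 × √0.19 = 0.252 and 0.578 × √0.20 = 0.258.

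| ρ | Follow-up values | Change | Baseline-adjusted |
|---|---|---|---|
| 0.5 | 0.58 | 0.58 | 0.50 |
| 0.7 | 0.58 | 0.45 | 0.41 |
| 0.8 | 0.58 | 0.37 | 0.35 |
| 0.9 | 0.58 | 0.26 | 0.25 |
| 0.95 | 0.58 | 0.18 | 0.18 |

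**Step 3: power at a true difference of 0.3 SD (assumed), by the t distribution.**

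| ρ | Follow-up values | Change | Baseline-adjusted |
|---|---|---|---|
| 0.5 | 31% | 31% | 39% |
| 0.7 | 31% | 47% | 53% |
| 0.8 | 31% | 63% | 68% |
| 0.9 | 31% | 90% | 92% |
| 0.95 | 31% | 99.6% | 99.7% |

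Adjustment removes the fraction ρ² of the variance. The follow-up t-test therefore loses more than half of the information only when ρ² > 0.5, that is, when ρ exceeds about 0.71.

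**Step 4: skewed markers.** Log-normal data were simulated with 48 per group, 20,000 runs per setting and a log-scale shift of 0.578 log-SDs, so that the log-scale t-test has about 80% power. The t-test on untransformed values has about 62%, 54% and 43% power at log-SD 1.0, 1.2 and 1.5. Repeat runs agree within about one percentage point. In a separate null simulation at log-SD 0.8 to 1.2, the type I error of the untransformed test was at or below about 5%. The cost is power, not validity.

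**The case against.** The strongest reply is that section 2.15 is a generic paragraph and does not prescribe the worst analysis one can read into it. Four parts of that reply need an answer.

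- **Baseline.** A reader might infer that the baseline value is ignored. The article does not say so. Sections 2.10 and 2.13.1 speak of alterations and changes in body composition, which fits a t-test on change. At ρ = 0.9 that test is nearly as good as the adjusted analysis (90% against 92% at 0.3 SD). This stands, but the tested quantity remains unstated, and at ρ = 0.5 change scores gain nothing over follow-up values.
- **Power.** A reader might infer that most of the power for body composition is wasted. That needs follow-up values to be tested, a high correlation and a modest effect. At ρ = 0.5 the comparison is 31% against 39%, and at a true effect of 0.58 SD the plain t-test already has 80% power. The correlation is not in the article.
- **Skewness.** A reader might infer that raw skewed values will be tested. Section 2.14 foresees that variables will be transformed. Its examples are not normalising transformations, but they are only examples. The skewness point also concerns inflammatory markers and adds nothing to the case on body composition.
- **Level of detail.** Model terms are often left to an analysis plan, which is not shown here. That would answer a complaint about silence, but section 2.15 is not silent. It names the test, and an analysis plan that follows it inherits the t-test.

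Nor is there a case against the test for remission. "Associations between categorical variables will be assessed using the chi-square test" names a valid test for a binary outcome in two arms. Replacing it with an adjusted model would be a preference, not a correction.

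**Conclusion.** The point holds as a choice of method that can be improved at almost no cost. For continuous outcomes the article names a t-test or ANOVA, although baseline and repeated values are collected. It leaves the tested quantity open and gives no distribution rule for group comparisons.

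Against a t-test on follow-up values, which detects 0.58 SD, baseline adjustment brings the detectable difference to between 0.50 SD (ρ = 0.5) and 0.18 SD (ρ = 0.95). High correlations are plausible for lean mass over 12 weeks, but that is an assumption. If change scores are tested, little is lost at high correlation. For CRP and calprotectin, the fall from 80% to about 62% to 43% power assumes a log-normal shape, log-SD 1.0 to 1.5 and no transformation.

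The article does not support a flat statement that the baseline is ignored, that most of the power is lost, or that the tests are invalid.

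**What to change.** In section 2.15, replace the t-test/ANOVA sentence for between-arm comparisons with wording such as: *Continuous outcomes will be compared between arms by a mixed model for repeated measures (SPSS MIXED) with arm, visit, arm-by-visit interaction and the baseline value; the arm difference at week 12 will be reported with its 95% confidence interval. CRP, IL-6 and calprotectin will be analysed on the log scale and reported as ratios of geometric means.*

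In section 2.2, delete the reference to matched data or define it as repeated measures within patient.

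Keep the chi-square test for remission.

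The cost is the wording and slightly more programming in the software already named. No new data, visits or patients are needed.
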